## Abstract

**Purpose:**

Adequate, needs-oriented psycho-oncological care contributes to reducing psychological distress in cancer patients and their relatives and improving quality of life. Regarding the precise determination of objective and subjective needs, there are often discrepancies in practice between the screening instrument completed by patients, the clinical impression of the treatment team, and the judgment of the psycho-oncology team.

**Methods:**

The present multicenter study “OptiScreen”, involving three German Comprehensive Cancer Centers (Hannover, Leipzig, Dresden), aims to professionalize psychosocial screening to enable targeted and needs-based allocation to psycho-oncological support. Optimization and professionalization of the screening process will be achieved by training of oncological nursing staff to improve the targeted identification of distressed patients and provide them with needs-based psycho-oncological care. The non-randomized pre-post study will include inpatients with gastrointestinal cancers from the visceral oncology centers at the three sites. First, the comparison group (CG) will be assessed of *N* = 300. After completion of nursing training, the intervention group (IG) with *N* = 600 patients will be evaluated by validated questionnaires.

**Results:**

The aim is to reduce barriers on both the patient and treatment side by promoting interdisciplinary dialogue and linking the screening with a personal consultation offer provided by the nurses, which should help to increase utilization and reduce patients' fears, shame and information deficits.

**Conclusion:**

It is not sufficient to establish a well-validated screening procedure, it also has to be feasible and useful in clinical practice. “OptiScreen” aims to improve the psycho-oncological care situation. In parallel, the study enables the professionalization of psycho-oncological care with the involvement of important professional groups (e.g. nursing) and thus aims to develop a “best practice model”.

**Supplementary Information:**

The online version contains supplementary material available at 10.1007/s00432-022-04368-5.

## Introduction

An adequate, needs-based psycho-oncological care contributes to reduce the burden of cancer patients and their relatives and to increase the quality of life (Faller et al. 2013). About half to two-thirds of outpatients and/or inpatients in Germany with various tumor entities show significant psychological distress (Mehnert et al. 2018; Peters et al. 2020), and approximately one-third of patients from in- and outpatient care facilities develop mental disorders (Mehnert et al. 2014). Previous research elicits cancer patients’ need for psycho-oncological care (Brix et al. 2008; Faller et al. 2016; Merckaert et al. 2010) and their beneficial effects on distress and quality of life (Faller et al. 2013; Kalter et al. 2018; Linden and Girgis 2012; Osborn et al. 2006; Rehse and Pukrop 2003). An implementation of psycho-oncological care for addressing psychosocial concerns of cancer patients is anchored in the S3 guideline "Psycho-oncological care of cancer patients" for Germany (Leitlinienprogramm Onkologie 2014) and in the National Cancer Plan (Bundesgesundheitsministerium 2012). As consented there, cancer patients can expect psycho-oncological support according to their needs (Herschbach and Mandel 2011). However, despite improvements in psycho-oncological care in Germany, defining the term “needs-based” remains a problem (Schalhorn and Herschbach 2016). The targeted identification of psychological distress in all cancer patients is still very incomplete and heterogeneous in clinical practice (Koehler et al. 2017). Clarification regarding the following questions is still required: Who is in need of psycho-oncological care and, above all, who determines this need and how?

It seems that neither the patient's self-assessment nor the medical team's assessment can satisfactorily explain these issues (Carlson et al. 2010). Thus, cancer patients in need of treatment and support may be overlooked. One consequence of this resulting psycho-oncological underuse is the recommendation to use screening questionnaires and thus to optimize the allocation to psychosocial measures (Schalhorn and Herschbach 2016; Stengel et al. 2021). According to a current best practice recommendation, for a successful establishment of a distress screening under routine clinical conditions, the following factors are necessary: “sufficient, trained and competent persons who actively take responsibility for screening are needed, as are detailed, standardized, and optimized procedures for implementation, evaluation, documentation, and referral” (p. 4, Stengel et al. 2021). Particularly in patients with surgical procedures, such as visceral oncology wards, there is often a lack of implementation of psycho-oncological care due to the focus on surgical procedures and somatic treatments (Burton and Parker 1997).

## Identification of psychosocial distress

Brief distress screening questionnaires should thus increase referral to psychosocial interventions (Andersen et al. 2014; Fitch et al. 2018). In accordance with the S3 guideline Psycho-oncology (Weis et al. 2022; Leitlinienprogramm Onkologie 2014), the following screening methods are recommended: Distress Thermometer (DT) (Mehnert et al. 2006a, b), Cancer Patient Stress Questionnaire (Book et al. 2011), Hospital Anxiety and Depression Scale (Herrmann-Lingen et al. 2011), and Patient Health Questionnaire (Kroenke et al. 2001) as well as Generalized Anxiety Disorder Scale-7 (Spitzer et al. 2006). However, the use of a screening procedure does not ensure that all persons screened as burdened are identified and also referred to psycho-oncological care. Often, patients are referred to psycho-oncology through their own initiative or through the initiative of a member of the medical team. This can lead to a not inconsiderable number of patients who need support not receiving it, because they may be too burdened to request it or, without a standardized approach, have difficulty finding appropriate help (Carlson et al. 2010). Furthermore, the use of screening does not seem to automatically lead to distressed patients also seeking psycho-oncological support (Funk et al. 2016). Only about 20–40% of highly distressed cancer patients make use of psychosocial services (Dilworth et al. 2014). In certified oncology centers, the utilization rate was 11% (Singer et al. 2013). Reasons for this are that patients often deny psychosocial problems and are afraid of stigmatization, "want to make it on their own" or "have to be strong", "do not want to be a burden to others—including the treatment team" or possibly do not understand the term "psycho-oncological support". In addition, there is a lack of information about the available services and unclear ideas about their benefits (Weis and Giesler 2016). In a multicenter, cross-sectional study in Germany by Faller et al. (2016) with 4020 cancer patients with different tumor entities only 38% of patients reported feeling sufficiently informed about psycho-oncological care. Furthermore, 36% requested more information about psycho-oncological support services. Moreover, insufficient communication between patients, physicians and nurses can be the cause. Thus, the implementation of a screening often has no influence on the use of psycho-oncology support (Braeken et al. 2013). Challenges of screening include overestimation or underestimation of mental distress as well as acceptance of the screening instrument. Furthermore, the mere use of a screening instrument cannot reliably measure emotional distress (Mitchell et al. 2011). However, if the screening (DT) is combined with a personal conversation and referral offers, the use of psycho-oncology support also increases (Carlson et al. 2010). In addition, the confidence as well as the skills of the clinician also have a positive impact on successful screening (Mitchell et al. 2011).

Moreover, there is a significant number of patients who seek support in the absence of mental comorbidity (Dilworth et al. 2014). The problem in determining need between subjective and objective need can lead to a patient not receiving support despite subjective suffering according to objective criteria (screening), whereas a person needs support according to objective criteria but does not express a subjective need for support. Standardized screening instruments usually cannot solve this problem.

Thus, despite the recommendation to provide needs-based psycho-oncological care as an integral part of comprehensive cancer treatment (Herschbach and Mandel 2011), which is obligatory for oncological centers and organ cancer centers after certification by the German Cancer Society, the on-site reality of psycho-oncological care structures is very heterogeneous and incomplete (Weis and Giesler 2016). Moreover, it should be taken into account that a considerable number of patients do not complete the screening at all. Nevertheless, there seems to be a need for optimization when it comes to implementation in practice. The instrument alone does not seem to be sufficient; it also requires "manpower" (Jacobsen and Jim 2008; Stengel et al. 2021). Barriers on the part of the treatment team might contribute to this problem, due to a lack of knowledge and skills regarding the use of a screening and lack of confidence in communication during the screening process (Mitchell et al. 2008).

The degree of implementation of screening procedures worldwide and also in Germany is very heterogeneous and often associated with a considerable organizational recording and evaluation effort. Screening should be quick, feasible, and easy to use in everyday routine. However, it should lead to rapid identification of patients in need of care and thus allow for high accuracy and simple evaluation, ensuring timely referral for psycho-oncology care and further clarification of indications. Improvements in care can only be achieved if additional staffing is provided. However, there are not enough resources available, especially in terms of highly qualified psycho-oncologists, to perform screenings. According to Mitchell (2013), screening reduces distress and improves quality of life only if barriers are removed. Significant barriers were identified as: lack of qualification and support of the treatment team, low acceptance by treatment providers, and lack of linkage between screening results and treatment.

The question arises whether other professional groups can also be trained in the implementation of a psychosocial screening and thus contribute to patients moving from screening to intervention. The S3 guideline on psycho-oncology also emphasizes the multiprofessional cooperation of different occupational groups (Stengel et al. 2021). However, nurses are less perceived in psycho-oncological care than other professional groups (Dautel 2015). There is close and frequent contact between patient and nurse, during which psychosocial stress is also discussed. However, nurses often avoid these discussions for fear of not behaving appropriately or not considering these discussions as a task area (Dautel 2015). This is not due to a lack of willingness on the part of the nurses to engage in such discussions, but rather to workload compression, lack of time and also a lack of competence, particularly in communication (Dautel 2015).

## The present study

Based on these preliminary findings, the primary objective of the study was derived: to optimize and professionalize the psychosocial screening process by training oncology nurses and developing an interdisciplinary care algorithm, thereby improving the targeted identification of mental distressed patients and the referral to psycho-oncology care as needed.

The postulated model of this study (Fig. 1) for the precise identification of distressed patients and for the provision of needs-oriented psycho-oncological care takes various processes into account. From all cancer patients, the mentally distressed patients have to be identified with the help of a screening. In the next step, these mentally distressed patients must also be provided with psycho-oncological care in line with their needs. The last step is to check whether the patients identified by the screening need psychosocial support through further psycho-oncological diagnostics—also for the diagnosis of mental disorders. In addition, barriers and obstacles need to be identified.

**Fig. 1 Fig1:**
[figure not shown]
Model for targeted identification of mentally distressed patients and referral to needs-based psycho-oncology care

In this context, one question is whether current screening is too unspecific in terms of identifying mentally distressed patients. On the other hand, there is also the question of what a "screener"—i.e., the person who carries out the screening—must be able to do. Important questions in this context are: How is the screening introduced? How is the screening evaluated? How are the results to be interpreted? What support does a patient need? When does the patient need to be consulted? "OptiScreen" aims to address precisely these issues and thus develop a "best practice model" based on the needs of cancer patients and the available resources. "OptiScreen" aims to train oncology nurses as "screeners" and, therefore, reduce personal and structural barriers in the screening process.

## Study objectives

The following questions and objectives are to be examined:

1. Acceptance of psycho-oncological screening: does the implementation of existing screening by trained oncological nurses lead to a higher acceptance of psychosocial screening among patients and the medical treatment team?

2. Targeted, needs-based referral to psycho-oncology: Does existing screening by trained oncology nurses lead to more targeted psychosocially distressed patients (identified by the screening cut-off value) to a psycho-oncological consultation? Are these patients mentally distressed (further psycho-oncological diagnostics)? Does the psycho-oncology team also report more targeted referrals of distressed patients to psycho-oncology?

3. Patient competence and satisfaction: Does the implementation of the screening by trained oncological nurses increase the knowledge and competence of the patients about psycho-oncological services, their acceptance and satisfaction?

4. Competence and satisfaction of the nursing staff: Does the implementation of the screening by trained oncological nursing staff increase the competence of the nursing staff, reduce possible fears or insecurities in contact with cancer patients and increase satisfaction?

5. Acceptance of psycho-oncological offers: does interdisciplinary collaboration lead to greater acceptance of psycho-oncological services and a reduction in obstacles and barriers?

6. Development of a tested training concept for oncological nurses to professionalize psychosocial screening.

7. Acceptance, satisfaction, and feasibility of training from the nursing perspective.

The OptiScreen-Training aims to improve (a) the identification of distressed patients and their referral to psycho-oncological support, (b) the patients’ satisfaction with the screening process and information regarding support options, (c) nurses’ acceptance of performing the screening, (d) nurses’ confidence and satisfaction regarding communication during the screening process, and (e) interdisciplinary communication between nurses and the psycho-oncological team.

The aim is to reduce barriers in psycho-oncological care for patients, and practitioners by developing a “best practice-model” for the screening process through training.

## Materials and methods

### Participants

The study population includes inpatients of the visceral oncology centers at the three sites. The following inclusion criteria are defined: (a) diagnosis of a malignant solid tumor in the context of a visceral oncological disease (according to the survey form of Onkozert (2018): intestine, pancreas, stomach, liver, esophagus); (b) a minimum age of 18 years; (c) cognitive ability to consent to study participation. The following exclusion criteria are established: severe physical, cognitive, and/or language limitations (not be able to fill in questionnaires in German language).

All nurses at the visceral oncology centers at the three sites are expected to participate in the training during their working hours. Nurses were offered the opportunity to complete an evaluation before and after the training.

In addition, psycho-oncologists will also be asked about their experience with the overall screening process before and after the training, as well as patient distress.

### Design

The study design is uncontrolled before and after pilot study. Measurement time points are a baseline measurement during the inpatient stay (t0) and a 3-month follow-up (t1 postal or online). As a comparison sample (CG, *N* = 300), screening data are collected 6 months prior to the introduction of the "OptiScreen-Training" on the same wards as after the introduction of the optimized screening, which thus corresponds to a care-as-usual (CAU) condition (Fig. 2). Care-as-usual refers to the identification of mentally distressed patients in the same way as is customary in their respective wards. Advantages of this approach are cost efficiency and practicality. After completion of the OptiScreen-Training, an additional *N* = 600 patients (intervention group, IG) will be surveyed at t0 and t1 (Fig. 2).

**Fig. 2 Fig2:**
[figure not shown]
Study design. CG = Comparison group; CAU = Care as usual; IG = Intervention group, t1 = 3 months follow-up (FU)

Positive ethics votes have been received from Hannover Medical School (8478_BO_K_2019), University Medical Center Leipzig (274/19-lk) and University Medical Center Dresden (EK 459,102,019).

### Sample size and power calculation

Based on the primary cases in the centers, *n* = 200 patients per center will be included in the IG over a recruitment period of 24 months. For the CG, *n* = 100 patients per center will be recruited. Thus, a study population of *N* = 300 patients in the CG and *N* = 600 patients in the IG can be assumed.

For the primary analysis of the main outcome variable (mental distress of patients), small to medium effects of the IG compared to the CG are assumed. Assuming an effect size of 0.3, a sample size of *n* = 190 evaluable persons each in CG and IG are required for the primary analysis to be able to prove the assumed effect with a power of 80% (G*Power). With a dropout of 50%, a total of *n* = 270 patients per group (CG and IG) resulting in a total of *N* = 540 must be recruited at t0.

For the study, the case numbers of the participating oncology centers result in *N* = 1,533 cases per year. For the recruitment period of 24 months, a total pool of *N* = 3,066 can thus be expected. Thus, after subtracting the expected dropout rate of 50%, *N* = 1,533 patients can potentially be recruited for the study. Thus, the target sample size of *N* = 600 (IG) can be considered feasible. Since the CG will be recruited before the IG, the targeted sample size of* N* = 300 can also be considered feasible.

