#### Statistical measures

First, the primary and secondary outcomes as well as all patient characteristics are analyzed descriptively together and separately for the two groups (means, standard deviations, frequencies). The primary outcome, psychological distress, is analyzed by ANCOVA (analysis of covariance) including variables such as tumor stage, age, and gender as covariates. This usually even increases the power of an ordinary *t* test. Missing values are replaced using multiple imputation. In sensitivity analyses, the results of the primary analysis are checked for consistency. Differences in secondary outcomes are evaluated between intervention and comparison groups or between appropriate subgroups analogous to the primary analysis using univariate or multivariate procedures or appropriate regression models. Depending on the distribution of the target parameter, binary or ordinal logistic mixed model regressions and linear mixed model regressions will be used. Before starting the analysis, the exact procedures are defined in a statistical analysis plan. Moderator as well as mediator analyses are used to identify barriers to take-up, as they can test complex relationships between several variables in the form of a priori models. The evaluation of the training will be analyzed using *t* tests (pre and post).

To control for possible selection effects that could lead to sampling bias, reasons for non-participation and sociodemographic and medical data of the non-participants will be analyzed. In this way, possible selection effects can be identified and the interpretation of results may be adjusted as necessary. Possible confounding variables are analyzed in inferential statistical analyses (e.g., regressions) using important covariates (age, gender, tumor entity, stage) as well as other theory-based influencing factors, e.g., physical comorbidities controlled.

Missing values due to drop-outs are replaced and can be predicted by means of multiple imputation, in that for the missing values, estimated values are used, which are calculated by distributing different predictors. This is done by taking all available relevant information of the data set into account and including random errors. The advantage is a low loss of information, since all variables remain included in the model. In addition, standard errors, which are moreover caused by the multiple repetition of the estimation process are randomly and realistically calculated and included.

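### 190 evaluable per group, 50% dropout and 270 per group to recruit cannot all be right: 50% dropout needs 380 per group, and 270 fits about 30%

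*Protocol article*

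**What the plan says.** All the figures stand in the protocol article, section *Sample size and power calculation*.

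- Effect and power: "Assuming an effect size of 0.3", with the sample chosen "to be able to prove the assumed effect with a power of 80% (G*Power"). Neither alpha nor sidedness is given.
- Evaluable patients: "a sample size of *n* = 190 evaluable persons each in CG and IG are required for the primary analysis".
- Recruitment derived from that: "With a dropout of 50%, a total of *n* = 270 patients per group (CG and IG"). The article adds this up to 540 patients needed at baseline.
- Planned enrolment, given separately: "a study population of *N* = 300 patients in the CG and *N* = 600 patients in the IG can be assumed". For the comparison group (CG): "For the CG, *n* = 100 patients per center will be recruited", over three centres. For the intervention group (IG), 200 per centre.

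The same section also uses 50% as a plain halving when it reduces a two-year pool of 3,066 cases to 1,533.

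Under *Statistical measures* the article adds: "The primary outcome, psychological distress, is analyzed by ANCOVA (analysis of covariance") with covariates, and multiple imputation of missing values. It puts no figure on what either does for power.

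**The concern.** The step from evaluable to recruited patients is a single division, and the printed result does not follow from the printed inputs. Half of 270 is 135, which is 55 short of the 190 that the preceding sentence calls required.

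The 270 per group is worded as the number that must be recruited, so a team whose accrual was slow could take it as the floor. The CG is the sensitive arm. It is collected before the nurses are trained, on the same wards, so patients missing from it could not be added later under usual care. The paragraph also makes a CG of 300 look as if it has 30 patients to spare over the requirement. At the stated dropout it yields fewer evaluable patients than the text asks for in that group.

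**Working it through.** **Inputs.** From the section *Sample size and power calculation*: d = 0.3 (read as a standardised mean difference), power 80%, 190 evaluable per group, dropout 50%, 270 per group to recruit, planned 300 and 600. Assumed, because not stated: two-sided 5%, with one-sided 5% as the range.

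**Step 1: try to reproduce 270.**
- Correct inflation, n/(1 − dropout): 190/(1 − 0.5) = 380 per group, 760 in total.
- Common mistake, n × (1 + dropout): 190 × 1.5 = 285. This does not give 270 either; it would need a start of 180, which is not in the text.
- Dropout implied by 270: 1 − 190/270 = 29.6%. Conversely, 190/0.70 = 271.4.

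No usual formula leads from 190 and 50% to 270. The gap to 380 is 110 per group.

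**Step 2: evaluable patients if 50% is right.**
- Stated requirement: 270 × 0.5 = 135 per group.
- Planned CG: 300 × 0.5 = 150.
- Planned IG: 600 × 0.5 = 300.

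**Step 3: power.** For a two-group comparison of means, the noncentrality is d × √(n₁n₂/(n₁ + n₂)). In the normal approximation, power is Φ(noncentrality − z), with z = 1.960 two-sided or 1.645 one-sided.

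| Evaluable | Noncentrality | Two-sided 5%, normal | Two-sided 5%, t test | One-sided 5%, normal |
|---|---|---|---|---|
| 190 / 190 | 0.3 × √95 = 2.92 | 83.2% | 83.1% | 90.0% |
| 135 / 135 | 0.3 × √67.5 = 2.46 | 69.3% | 69.0% | 79.4% |
| 150 / 300 | 0.3 × √100 = 3.00 | 85.1% | 84.9% | – |

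With 135 per group, 80% power at two-sided 5% is reached only for a difference of (1.960 + 0.842) × √(2/135) = 0.34.

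**Step 4: the 190 itself.** For d = 0.3 and 80% power at two-sided 5%, the t test needs 176 per group. The printed 190 is therefore slightly generous. It also points to a two-sided test: it gives 83% two-sided but 90% one-sided.

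**Step 5: the planned 1:2 design against the 190.** The equal-group equivalent of 150 and 300 is 2 × 150 × 300/450 = 200 per group. That exceeds 190, although 150 taken alone does not.

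**Step 6: if about 30% is right instead.** 270 × 0.70 = 189 evaluable per group, so the 270 holds. The planned groups would leave 300 × 0.70 = 210 and 600 × 0.70 = 420, both above 190.

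**The case against.** The strongest reply is that no planned trial has 69% power. The targets throughout the article are 300 and 600, and nothing provides for stopping at 540. This stands. The 69% describes only a trial that relied on the 270.

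Second, the slip may lie in the 50% and not in the 270. At about 30% dropout the 270 is right and nothing is short. The other use of 50% in the section reduces a case pool to those who might be recruited. That is non-participation before t0, so it does not settle the loss expected afterwards. This also stands: the text shows an inconsistency and does not show which figure is wrong. It prints 50% next to 270, however, and gives no other rate.

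Third, alpha is not stated, and one-sided 5% brings the power at 135 per group to 79%, close to 80%. This is a fair limit on the size of the effect. It does not reconcile the figures, since 135 is not 190 on either reading.

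Fourth, covariate adjustment and multiple imputation might change the power. They might, but the article quantifies neither, and its own calculation counts evaluable persons.

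A reader might also infer that 190 is wrong because 176 would do. The documents do not support that. The 190 meets the 80% target with a small margin, and a condensed article may leave the reason for the margin to the full protocol.

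**Conclusion.** The point holds as an internal inconsistency in a printed sample size figure. The 190 evaluable, 50% dropout and 270 to recruit cannot all be true: at 50% the requirement is 380 per group (760 in total), 110 per group more than stated, and 270 goes with about 30%.

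The effect on power is conditional. If 50% is right and recruitment stopped at 270 per group, power for d = 0.3 would be about 69% at two-sided 5% (79% at one-sided 5%), not 80%. These are unadjusted, complete-case figures that rest on an assumed alpha.

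A reader might infer that the trial as planned is underpowered, or that its CG is too small. The documents do not support this. With 300 and 600 recruited and 50% dropout, power is about 85% at two-sided 5%, because the larger IG makes up for the smaller CG. The CG's 150 evaluable miss the 190 that the text asks of each group, but that is a mismatch of wording: 190 is an equal-allocation figure and the design is 1:2. The paragraph needs correcting; the enrolment targets do not.

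**What to change.** Reword the one paragraph in the section *Sample size and power calculation*:

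1. Replace 270 per group and 540 in total with 380 and 760, labelled as the requirement for equal groups at 50% dropout. Alternatively, keep 270 and 540 and state the dropout of about 30% for which they hold.
2. State alpha and whether the test is one- or two-sided.
3. Give the power of the design actually planned: 300 and 600 recruited, 150 and 300 evaluable at 50% dropout, about 85% for d = 0.3 at two-sided 5%, unadjusted. If the dropout is corrected to about 30%, recompute this from 210 and 420.
4. Say that 190 per group assumes equal allocation, so that a planned CG of 300 does not appear to contradict a requirement of 380 per group.

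The cost is a few sentences. The 190, the 300/600 targets and the analysis stay as they are, and no further patients are needed.
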